# The effectiveness and health-economic evaluation of “Partner in Balance,” a blended self-management program for early-stage dementia caregivers: study protocol for a cluster-randomized controlled trial

**DOI:** 10.1186/s13063-023-07423-9

**Published:** 2023-06-22

**Keywords:** Dementia, Economic evaluation, Cost-effectiveness, Cost-utility, Online intervention, Cluster RCT, Blended care, Informal care, Self-efficacy

## Abstract

**Background:**

Informal caregivers of people with dementia are crucial in dementia care. However, they are insufficiently supported and report caregiver burdens, which urges the need for cost-effective interventions aimed at supporting caregivers. This paper presents the design of a study evaluating the effectiveness, cost-effectiveness, and cost-utility of a blended self-management program for early-stage dementia caregivers.

**Methods/design:**

A pragmatic, cluster randomized controlled trial with a shared control group will be conducted. Participants will be informal caregivers of people with early-stage dementia and will be recruited by local care professionals. Randomization will be carried out at the level of the care professional level in a ratio of 35% to 65% (control arm vs. intervention arm). Participants in the control arm will receive care as usual and the intervention arm will receive the blended care self-management program “Partner in Balance” within a usual care setting in the Netherlands. Data will be collected at baseline and at 3-, 6-, 12-, and 24-month follow-ups. The primary outcome for effectiveness (part 1) is care management self-efficacy. For the health-economic evaluation (part 2) total care costs and the quality of life for individuals with dementia (cost-effectiveness) and quality-adjusted life years (cost-utility) will be the base case analysis. Secondary outcomes (parts 1 and 2) will include depression, anxiety, perceived informal caregiving stress, service-use self-efficacy, quality of life, caregivers’ gain, and perseverance time. A process evaluation (part 3) will investigate the internal and external validity of the intervention.

**Discussion:**

In this trial, we plan to evaluate the effectiveness, cost-effectiveness, and cost-utility of “Partner in Balance” among informal caregivers of people with dementia. We expect to find a significant increase in care management self-efficacy, and the program to be cost-effective, and provide valuable insights to stakeholders of “Partner in Balance.”

**Trial registration:**

ClinicalTrials.gov, NCT05450146. Registered on 4 November 2022.

**Supplementary Information:**

The online version contains supplementary material available at 10.1186/s13063-023-07423-9.

## Introduction

### Background and rationale

The global economic impact of the total 55 million people living with dementia [1] had an estimated cost of US $1.3 trillion in 2019 [2]. Nearly half of these total dementia care costs were associated with the support and assistance provided by members in the close social environment, known as informal care [2]. In addition to the economic impact, providing informal care to a person with dementia (PwD) negatively influences the caregiver’s general well-being in terms of self-efficacy, caregiver burden, quality of life, and life satisfaction. Caregiving also influences their physical and mental health, more specifically it can lead to stress, anxiety, and depression [3–5]. European healthcare systems insufficiently protect informal caregivers sufficiently against the negative impact of informal care [6, 7]. This is demonstrated by the majority of informal caregivers urging a need for additional support [8]. This unmet need for support for caregivers in combination with the expected increase in dementia’s prevalence and total dementia costs [2] urgently calls for cost-effective interventions aimed at supporting informal caregivers to manage living well at home.

Prior research indicated that non-pharmacological multi-component interventions can reduce caregiver burden [9–11], which is a significant predictor for the institutionalization of the PwD [12, 13]. This was substantiated by reported delayed institutionalization rates in several earlier studies on multi-component interventions [9, 11, 14]. Institutionalization can also be predicted by the health-related quality of life of the caregiver [15]. Prior research demonstrated that similar interventions could effectively target this predictor [9, 16]. Therefore, these interventions could significantly lower total dementia healthcare costs by delaying the institutionalization of the PwD. In addition, informal caregivers’ healthcare usage could also be lowered because it is associated with caregiver depression [17], which is positively influenced by internet-based or technology-based interventions in randomized trials [18, 19]. Therefore, blended e-health interventions consisting of a combination of online therapy and in-person treatment, aimed at informal caregivers, consisting of education, information, and training in self-management skills could potentially be cost-effective due to their efficient use of resources.

The Partner in Balance (PiB) [20] intervention is an online psychoeducation and behavioral modeling intervention for informal caregivers of PwD in the early stage of the disease, coached by a care professional. In earlier research [21], the effectiveness of PiB over an 8-week follow-up period has been demonstrated to significantly improve self-efficacy, mastery, and quality of life compared to usual care in an 8-week randomized controlled trial (RCT) in informal caregivers of persons with mild cognitive impairment (15%), Alzheimer’s dementia (41%) or other dementia types (44%) in the setting of memory clinics and ambulatory mental health clinics [21]. Currently, the effectiveness in the longer term and the cost-effectiveness of the PiB intervention are still unknown. However, this is essential information so that scarce healthcare resources can be utilized as efficiently as possible while maintaining high-quality care that is equal and equitable. This research protocol describes a proposed pragmatic cluster RCT to evaluate the effectiveness (part 1) and to perform a health-economic evaluation (part 2) of the blended care self-management program PiB. In addition, the method for a process evaluation (part 3) will be described.

### Objectives

This proposed research consists of three parts: (1) an effectiveness analysis, (2) a health-economic evaluation, and (3) a process evaluation.

#### Part 1: effectiveness

The primary objective is to estimate the effectiveness of the blended care program PiB compared to usual care over 12 months. We hypothesize that the care management self-efficacy in terms of CSES of caregivers who receive PiB will have a significantly better self-efficacy than that of caregivers who only receive usual care. The secondary objective is to explore the effect of PiB on the primary outcome care management self-efficacy at 24-month follow-up and on the secondary outcomes: perseverance time, quality of life, service-use self-efficacy, positive experiences related to informed care, experienced care burden, anxiety, caregiver gains, and depression up to 24-month follow-up.

#### Part 2: health-economic evaluation

The health-economic evaluation consists of two primary objectives: (1) to estimate the within-trial cost-utility and uncertainty of PiB compared to usual care from a societal perspective over a time horizon of 12 months using EQ5D5L-based quality-adjusted life years and care use from both caregiver and PwD summed, and (2) to conduct a budget impact analysis. We expect PiB to be cost-effective. In addition, the health-economic evaluation includes the three following secondary objectives: (1) to estimate the within-trial cost-effectiveness and uncertainty of PiB compared to usual care from a societal perspective over a time horizon of 12 months, with effectiveness measured in terms of QOL-AD; (2) to perform a cost-consequence analysis to describe all relevant health outcomes, quality of life, and disaggregated costs categories; (3) to explore the health-economic outcomes of PiB over 24 months; and (4) to estimate the lifetime cost-utility and uncertainty of PiB compared to usual care from a societal perspective using a decision-analytic model with extrapolated trial effects.

#### Part 3: process evaluation

A process evaluation aims to evaluate the internal and external validity of this research. This will be attempted by monitoring the research’s sampling process, and the intervention quality (intervention adherence and the experiences of persons with dementia, caregivers, and care professionals with PiB).

## Methods/design

A pragmatic, cluster RCT design will be used to study participants’ longitudinal outcomes at baseline (T_0_), at 3 months (T_1_), 6 months (T_2_), and 12 months (T_3_) follow-up, and partly at the 24-month follow-up (T_4_), in the control and intervention arm. The control arm will be shared with another collaborating study (called “Eerder-Erbij”) at the Vrije Universiteit of Amsterdam (the Netherlands). Concretely, this entails that the two studies share their recruitment efforts by each supplying part of the targeted control arm participants but recruit their own intervention arm participants to compare their respective interventions to the shared control arm. The collaborating study will apply the same inclusion criteria, same study procedures, and evaluate the same outcomes over time. See Fig. 1 for the participant's flow diagram of the research. This study protocol follows the Standard Protocol Items: Recommendations for Interventional Trials (SPIRIT) guidelines [22] (see Additional file 1).

**Fig. 1 Fig1:**
[figure not shown]
Participant flow diagram according to Consolidated Standards of Reporting Trials (CONSORT)

### Study setting

Study participants will be recruited in primary care by their local care professionals (e.g., case managers dementia, and home nurses) in the Netherlands.

### Eligibility criteria

In order to be eligible to participate in this study, a participant must meet all of the following inclusion criteria: (1) the subject is an informal caregiver of a person with early-stage dementia; (2) the PwD, for whom they care, has a diagnosis of dementia (self-reported or known by the recruiting organization) or underdiagnosed dementia (no formal diagnosis but symptoms of dementia, as judged by the recruiting care professional, based on their professional opinion and experience); and (3) the PwD is not yet receiving formal care related to personal activities of daily living (ADL) on account of his/her dementia more than once a week (defined by receiving assistance from a paid worker (e.g., health or social care worker) such as help with dressing/undressing, washing/bathing/showering, toileting, feeding/drinking, taking medication or attending day activity or daycare center).

An informal caregiver who meets any of the following criteria will be excluded: (1) participating in another trial with similar objectives as this research; (2) younger than 18 years; (3) no basic internet skills; (4) no access to the internet at home; (5) already received the PiB program; (6) receiving a similar support program; and (7) not able to follow COVID19 instructions. The subject will also be excluded from participation if the informal caregiver or the PwD: (1) has a major mental or physical illness; (2) does not have a minimum understanding of the Dutch language; or (3) the dementia of the PwD is caused by human immunodeficiency virus (HIV), acquired brain impairment, down syndrome, chorea associated with Huntington’s disease, or alcohol abuse.

### Recruitment

Study participants will be recruited through care professionals with ≥ 1 year of experience with the target population and no prior experience with PiB who are already in contact with the targeted study population (i.e., informal caregivers of a person with early-stage dementia). These care professionals will be recruited from several home care organizations within the Netherlands via the Dutch Dementia network (https://www.dementienetwerknederland.nl/) and via contacts of the Alzheimer Center Limburg. Participating professionals will be asked to screen their caseload for about 1–5 eligible informal caregivers, provide them with introductory information on PiB and, if are interested, send their contact details to the research team. The potential study participants will then be called by the research team and, if they are interested, receive a study information letter and study consent form. Potential participants will be contacted again within 2 weeks. When the caregivers are willing to participate, they will be screened during a short telephone interview to check the inclusion and exclusion criteria. Participation starts after the research team has received written informed consent from the informal caregiver. Participants will be asked separately for consent to reuse their data for future research (participation is thus possible without consent for data reuse).

### Randomization

Before randomization, the participant will complete the baseline assessment. Then, cluster randomization on the level of the care professionals will be applied. Therefore, professionals and their corresponding set of 1–5 recruited participants will be randomly allocated either to the intervention arm (receives the PiB program in addition to usual care) or to the control arm (only receives usual care) by a spreadsheet random number generator. Because of the shared control arm design, fewer control arm participants need to be recruited than intervention participants. Therefore, in this study, 65% of participants will be allocated to the intervention arm and 35% to the control arm. Stratified randomization [23] will be utilized to ensure that distribution among care professionals within each organization will be as even as possible. Finally, due to variations in the cluster sizes, deviations could occur for the target sample size. In case the allocation diversion is larger than 10% than the desired allocation of 65/35 (e.g., 77% was allocated to the intervention arm at some point during recruitment), the probability to be allocated to the under-allocated arm (e.g., the control arm) will be set to 0.80. The randomization process, enrollment of participants, and assignment of participants to their arms will be executed by the main researcher ([name]). Due to the nature of the intervention in this research, blinding of the participant, care professional, outcome assessor, and data analyst will not be attempted because of pragmatic limitations.

#### Matching

To minimize any selection bias because of the shared control group with the collaborating study, control participants will be matched. For the matching, an additional 15 control participants will be recruited to allow for a larger pool of control participants to match from. The best-fitted controls from the collaborating study will be included in our control arm to reach the targeted sample size of the control arm. Matching will be done on the following characteristics: care organization (size and type); care professional (type and educational level); participant informal caregiver (age, sex, educational level, and informal care hours); PwD (age, sex, educational level, and dementia severity); and the preferences, beliefs, and experiences of e-health or face-to-face contact of the informal caregivers and professionals. Additionally, propensity scores will be calculated based on the questions handling restraint of the informal caregivers due to COVID-19.

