### Sample size

The sample size calculation was based on an earlier short-term effectiveness study of PiB [21] that targeted a similar population and used the CSES as a primary effectiveness outcome measure. With an assumed cluster size of 10 informal caregivers, alpha 0.05, power 0.80, and 25% drop-out at 6 months, the total sample size is 126 participants (with 63 in the control arm and 63 in the intervention arm). However, the sample size will be recalculated based on the CSES after 52 participants have completed their baseline assessment so that the targeted sample size can be adjusted with updated information on the standard deviation.

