#### Part 1: effectiveness

Prior to the analysis, the data will be examined for missing data and described. To verify the randomization procedure, potential differences in the baseline characteristics of the intervention and control arm will be examined using t-tests for continuous variables and the chi-squared (*X*^2^) test for categorical variables. A mixed generalized linear model (GLM) will be fitted to the care management CSES score (dependent variable) based on the recommended model of Bell and colleagues [42]. The model will include the following independent variables: trial arm, time (categorically), and the interaction between the trial arm and time. Time will be treated as a categorical variable because Donohue and Aisen [43] discuss that data from early in the trial has less influence in a categorical time model framework. As PIB is aimed at sustainable effects over a longer period, we are interested in the outcome at the end of the trial. Therefore, we believe this approach fits better than treating time as continuous. A link function and distribution family will be chosen that best fits the data (in terms of normality of residuals and linearity). A random intercept will be employed to acknowledge the hierarchical structure of the data (observations clustered within participants, and participants clustered within professionals). An unstructured covariance matrix for residual errors will be applied. If the p-value related to the intervention coefficient is less than 0.05 (2-sided) the intervention will be considered to have a statistically significant effect on the primary outcome, which would confirm our hypothesis. For this analysis, any missing data will be assumed missing at random (MAR) and handled by the mixed model.

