For trials with cluster randomization, the potential for selection bias is high because the allocation to treatment is usually predetermined for each member of the cluster, which is a common but undesired practice [53, 54]. This could be demonstrated when a care professional who has foreknowledge of their allocation to the PiB intervention arm likely approaches potential participants in a different way than a care professional who known has been allocated to the control arm. Therefore, in this study, clusters will be randomized after inclusion and baseline measurement to eliminate foreknowledge that can lead to selection bias. During the randomization process, stratified randomization will be used to limit potential selection bias due to a possible association between the organization and the impact of the care received by the informal caregiver [23].

The shared control group will increase the feasibility of the recruitment of participants, which is often a serious challenge in research. However, a shared control group also brings a risk of selection bias. We expect that the participants in the collaborating study are a slightly different selection of the same target population for the following reasons: (1) they will be recruited through a different type of collaborating organizations and (2) they might have different participation considerations for the collaborating study, considering it will be a peer-based group intervention. To prevent this selection bias, matching will be executed to control for these anticipated differences.

The study may yield some limitations. A limitation is that the PiB intervention is only aimed at informal caregivers with internet skills. Therefore, the results of this study will not be generalizable to all informal caregivers. Another limitation is that, due to the nature of the intervention, participant and care professional blinding was considered not feasible by the research team. The absence of blinding could lead to a placebo effect.

In conclusion, the results of this research will add to the scientific knowledge of the effectiveness of the blended care intervention “Partner in Balance.” The program is hypothesized to improve informal caregivers’ self-efficacy and is expected to be cost-effective. This study will provide valuable insights to informal caregivers, PwD, policymakers, care insurers, and care professionals into the effectiveness of PiB for supporting informal caregivers of PwD.

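### At target, about 46% of the control arm is not randomized against PiB, yet the stated primary model adjusts for neither control source nor the matching variables

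*Protocol article*

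**What the plan says.** All references are to the Protocol article.

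- **Sample size:** "the total sample size is 126 participants (with 63 in the control arm and 63 in the intervention arm". The stated inputs are: "With an assumed cluster size of 10 informal caregivers, alpha 0.05, power 0.80, and 25% drop-out at 6 months".
- **Randomization:** "in this study, 65% of participants will be allocated to the intervention arm and 35% to the control arm". The section explains the uneven split by the shared control arm.
- **Matching:** the shortfall in controls is filled from the other study: "The best-fitted controls from the collaborating study will be included in our control arm to reach the targeted sample size of the control arm". Matching uses features of the organization, the professional, the caregiver (age, sex, education, care hours), the person with dementia, and attitudes to e-health. Baseline CSES is not listed. In addition, "propensity scores will be calculated based on the questions handling restraint of the informal caregivers due to COVID-19"; how these scores will be used is not said. Fifteen extra controls are to be recruited to widen the pool, without saying by which study.
- **Discussion:** "We expect that the participants in the collaborating study are a slightly different selection of the same target population". The reasons given are a different type of recruiting organization and different motives for joining, because the other intervention is a peer group. A joint three-arm randomization was considered and not adopted.
- **Part 1: effectiveness (statistical analyses):** "The model will include the following independent variables: trial arm, time (categorically), and the interaction between the trial arm and time". Random intercepts cover participant and professional. The decision rule is worded "If the p-value related to the intervention coefficient is less than 0.05 (2-sided", and no time point or contrast is named.

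**The concern.** Randomization protects the comparison of PiB participants with the controls randomized in this trial. It does not protect the comparison with controls brought in from another study. Those people may be randomized within their own trial, but not against PiB.

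The protocol recognizes this and names matching as the remedy. The primary model then handles all controls as one randomized group, with no matching variable, no propensity score and no term for the study of origin. Any prognostic difference that imperfect matching leaves behind is averaged into the control mean in proportion to the external share. It becomes part of the estimated PiB effect, in either direction. The professional-level random intercept accounts for correlation within professionals; it does not remove a systematic shift between the two sources.

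At stake is whether the primary result can be read as a cluster-randomized effect.

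**Working it through.** **1. The plan's own figure.** The total of 126 cannot be reproduced, because the effect size, SD and ICC are not given. One partial check is possible: 47 evaluable per arm inflated for 25% drop-out is 47/0.75 = 62.7, or 63. The rest of this check uses only the 63/63 split.

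**2. External share of the control arm.**

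- Recruited in this trial: 63/0.65 = 96.9.
- Own controls: 96.9 × 0.35 = 33.9, about 34.
- External controls: 63 − 33.9 = 29.1, about 29, and 29.1/63 = 46%.

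With equal arms the share is 1 − 35/65 = 46% whatever the total. The planned sample size recalculation therefore changes the counts, but not the share unless the arms cease to be equal. Drift does change it. Reading the Randomization section's 10% tolerance as percentage points:

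| Realized allocation | Own controls | External controls | External share |
|---|---|---|---|
| 55/45 | 51.5 | 11.5 | 18% |
| 65/35 | 33.9 | 29.1 | 46% |
| 75/25 | 21 | 42 | 67% |

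If all 15 extra controls were randomized here and all were used, 63 − 34 − 15 = 14 would be external (22%), but this no longer fits 65/35.

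**3. Bias and type I error (illustration).** Let s be the shift in external controls, in SD units, that survives matching and any baseline contrast. It is an assumption; the protocol gives no figure.

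- Bias = 0.46 × s.
- SE = √(2 × DE/47.25), where 47.25 = 63 × 0.75 and DE = 1 + 9 × ICC for clusters of 10.
- ICC 0 (assumed): SE = 0.206, and the effect detectable with 80% power is 0.58 SD.
- ICC 0.05 (assumed): SE = 0.248, and the detectable effect is 0.69 SD.
- Two-sided type I error = 1 − Φ(1.96 − bias/SE) + Φ(−1.96 − bias/SE).

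| s | Bias | Type I error, ICC 0.05 | Type I error, ICC 0 |
|---|---|---|---|
| 0.2 SD | 0.09 SD | 0.066 | 0.073 |
| 0.3 SD | 0.14 SD | 0.086 | 0.103 |

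The SE is that of a comparison at one time point. A change contrast would have another SE, depending on the correlation between T0 and 12 months, which is not given.

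**4. Is a randomized-only comparison usable?** The SE ratio of 63 v 33.9 to 63 v 63 is √[(1/63 + 1/33.9)/(2/63)] = 1.195. For an effect that the full comparison detects with 0.80 power (noncentrality 2.80), power is Φ(2.80/1.195 − 1.96) = Φ(0.38) = 0.65.

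**The case against.** The best defence is the longitudinal model. CSES is measured at T0, and time is categorical with an arm interaction. If T0 is in the outcome vector, which the article implies but does not state, the 12-month interaction contrast cancels any constant baseline CSES difference between control sources. This stands. A reader might infer that the analysis is wholly unadjusted and that baseline CSES differences pass straight into the effect; the text does not support that. What remains exposed is differential change over time and imbalance in other prognostic factors. The protection also depends on which coefficient is tested: with T0 as reference, the arm main effect is the baseline difference itself.

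Leaving baseline CSES out of the matching list is likewise not plainly an error. Matching on a noisy baseline score across populations that differ can bring regression to the mean. It matters here because nothing in the model, as worded, makes the baseline handling explicit.

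Three further readings are tempting and go beyond the document:

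- That about 29 of a pool of 44 must be kept. This assumes all 15 extra controls come from the collaborating study, which is not said.
- That external controls could be picked after outcomes are known. The article is silent on timing, and the listed matching items are characteristics, not outcomes.
- That no randomized-only analysis exists. A sensitivity analysis may stand in a SAP that is not shown, so its absence from an article is not a fault.

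There are also real mitigations. The two studies share eligibility criteria, procedures and outcomes, the abstract discloses the shared control group, and the difference is expected to be slight. These make a large shift less likely; they do not make the sources exchangeable.

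**Conclusion.** The point holds for the model and matching plan as written. A substantial share of the control arm is unrandomized against PiB, the authors anticipate that it differs, and the stated primary model takes no account of where controls came from or what they were matched on. The economic models in the same article do adjust for baseline value, so the contrast is with the plan's own practice.

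The 46% share is arithmetic from the stated targets, assumes 65/35 is achieved, and ranges from about 18% to 67% at the drift limits. The type I error of about 7% to 10% is an illustration: it rests on an assumed residual shift of 0.2 to 0.3 SD and an assumed ICC of 0 to 0.05. It shows that a modest shift would matter; it does not show that bias of that size will occur.

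**What to change.** 1. Adjust the primary model for the main matching variables, or for one parsimonious propensity score for control source built from them and not from the COVID-19 items alone. Leave out variables without overlap. Organization type may be one, since external controls are expected from a different type of organization.
2. Handle baseline CSES once. Either keep T0 in the outcome vector and name the 12-month arm-by-time contrast as the primary test, or enter baseline CSES as a covariate and remove T0 from the outcome.
3. Prespecify the comparison restricted to participants randomized in this trial (63 v about 34) as the key sensitivity analysis. Simply adding a source term with its time interaction to the pooled model would amount to nearly the same comparison, because every PiB participant comes from this trial. It is therefore a way to run this check, not a substitute for step 1.
4. State that external controls are selected on baseline data only.

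The cost is analysis-plan wording and some extra analysis with data already collected. The downsides are that the randomized-only estimate is less precise (power about 0.65 against 0.80) and may disagree with the pooled one, and that about 29 external controls support only a small propensity model. With the last recruitment expected in May 2024 and the last follow-up in May 2026, the protocol's timeline left room to fix this before final data.
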